### The Present Study

The aim of this work is to examine the efficacy of several types of interventions, in therapeutic and cost-effectiveness terms, for the treatment of patients with EDs. The different interventions are the following: brief psychological treatment based on UP; conventional psychological treatment; conventional psychological treatment plus pharmacological treatment; minimum intervention based on basic psychoeducational information, counseling and bibliotherapy; and pharmacological treatment.

We hypothesize that “conventional psychological treatment plus pharmacological treatment” will be the most effective treatment, but “brief psychological treatment based on UP” will be the most efficient treatment (cost-effectiveness). Besides, we expect that psychological treatment (brief and conventional) will be more effective than pharmacological treatment, but less effective than “conventional psychological treatment plus pharmacological treatment,” and that “brief psychological treatment” will be as effective as “conventional psychological treatment” but more efficient than this one. Finally, we think that “minimum intervention based on basic psychoeducational information, counseling, and bibliotherapy” will be more effective than pharmacological treatment but will get worst results that different versions of psychological treatment.

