Taking into account these results, a generalized medium effect size of 0.6 (Cohen’s *d*) was assumed to detect differences between the interventions and TAU. Due to software to calculate the sample size for analysis using mixed linear models is not available, we established the sample size for analysis of variance using the *f* index trough G^∗^Power. Therefore, we assumed an effect size of 0.3 (*f* index), equivalent to Cohen’s *d* = 0.6. Thus, with a statistical power of 0.80 and an alpha level of 0.05, a total sample of 140 participants will be required (28 subjects in each group). With the objective of controlling the lack of participants throughout intervention and evaluation process, based on previous studies (Farchione et al., 2012; Ito et al., 2016), we assumed an abandonment rate of 15%. Consequently, we require to include 165 participants in our study (33 participants per group).

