## Proposed Analysis

The data will be analyzed following both intention-to-treat (ITT) and per protocol approaches. Firstly, ANOVA or chi-squared will be performed to compare the demographic variables and outcomes measures at baseline. Second, to examine longitudinal changes over time (baseline, posttreatment and follow-up) and between-group differences on these changes we will use linear mixed models, inasmuch as these models are more accurate than repeated-measures ANOVAs (Gueorguieva and Krystal, 2004). In the ITT analysis (all patients randomized are included in the analysis), the incomplete or missing data will be considered using the maximum likelihood estimation method. Additionally, Cohen’s *d* will be calculated to determine the size of between-group effects. Last, we will estimate the Incremental Cost-Effectiveness Ratio (ICER) to compare the relationship between costs and effectiveness of different interventions.

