## Anticipated Results

This research protocol pretends to highlight the importance of adapting treatments to real contexts of application, and their adjustment to brief formats of limited time that maximize the cost-benefit of implemented care, as other authors suggest (Kazdin, 2008; Moriana and Martínez, 2011), besides contributing to the dissemination of psychological treatments in primary and specialized care.

The principal objective of this work is to examine the effectiveness and the efficiency of the brief psychological treatment in a sample of patients with EDs, compared to other four treatments: conventional psychological treatment, conventional psychological treatment plus pharmacological treatment, minimum intervention based on basic psychoeducational information, and pharmacological treatment. Although we think that psychological treatment (brief and conventional) will be more effective than pharmacological treatment, as suggested by previous results with patients with EDs (Heuzenroeder et al., 2004; Watts et al., 2015), we expect that “conventional psychological treatment plus pharmacological treatment” will be the most effective treatment. This findings will be compliant with other studies that indicate that the combined treatment is superior in efficacy to CBT and pharmacotherapy alone in both anxiety disorders (Furukawa et al., 2007; Van Apeldoorn et al., 2008) and depression (Keller et al., 2000; Pampallona et al., 2004).

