Due to brief psychological therapies have obtained similar results to conventional psychological therapies (Miller, 2000; Bloom, 2001; Lyons and Low, 2009; Nieuwsma et al., 2012), proving effective in reducing anxious-depressive symptoms (Koutra et al., 2010; Bernhardsdottir et al., 2013; Saravanan et al., 2017), and UP have demonstrated its effectiveness to the treatment of EDs (Barlow et al., 2004; Brown and Barlow, 2009; Farchione et al., 2012), we hope that brief psychological treatment based on UP will be the most efficient treatment and as effective as conventional psychological treatment. However, although there is evidence suggesting that the patient’s improvement, after being treated with brief psychological therapies, remains long after treatment (Hamdan-Mansour et al., 2009; Vázquez et al., 2012), some authors question the maintenance of long-term results (Seekles et al., 2013). Therefore, the results of this study will be added to the evidence of efficacy for brief psychological treatments for EDs right after the treatment and at 6-month follow-up.

By last, we think that “minimum intervention based on basic psychoeducational information, counseling and bibliotherapy” will be more effective than pharmacological treatment for participants included in this study, but will get worst results that different versions of psychological treatment. Due to this kind of interventions are not sufficiently represented in controlled research (Labrador et al., 2000), the results of this work could contribute to the dissemination of minimum psychoeducational interventions to address the treatment of EDs in the PC context.

In last years, new intervention modalities are gaining consensus for the treatment of mental disorders, such as the stepped care approach. This treatment modality consists of apply progressively low and high intensity interventions (Turpin et al., 2008) and is based in two fundamental principles. Firstly, the treatment should produce positive results with the least burden for the patient. Secondly, the results of the patients should be reviewed systematically to decide about the need to move to another level of treatment.

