## Limitations

This study presents several limitations. The first one is related to the design of the study, since the interventions included in the protocol are composed by a different number of sessions. Nevertheless, it is necessary to include interventions with different length to determine whether the treatment effect varies depending on the intensity and duration. Besides, except for the “brief psychological treatment based on UP” group, the number of sessions or weeks of interventions within a certain group could vary from one patient to another. However, we will make sure that each patient is evaluated 6 months after the end of the treatment (follow-up assessment).

As a limitation inherent in this type of studies, considerable dropout rate during the intervention process are expected, as well as a substantial missing data to follow-up. Nevertheless, participants will be animated by phone or email to continue with the treatment or to participate in the follow-up assessment. In addition, the anxious-depressive symptoms could be attenuated by the passage of time.

Other limitations may be related to the recruitment difficulties. Due to the participants must be diagnosed with a DSM-5 disorder and must meet predetermined cutoff points, may be recruitment problems related to the difficulty that participants completely met the eligibility criteria. Besides, patients may refuse to be treated by a different intervention than usual.

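### The ICER, the only efficiency measure named, is undefined at the equal effect hypothesised for brief versus conventional treatment; incremental net benefit should decide instead

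*Protocol article*

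**What the plan says.** Efficiency is not a side question here. Anticipated Results states: "The principal objective of this work is to examine the effectiveness and the efficiency of the brief psychological treatment in a sample of patients with" emotional disorders, compared with the other four treatments. The Present Study expects that brief treatment "will be as effective as “conventional psychological treatment” but more efficient than this one", and Anticipated Results repeats it: "we hope that brief psychological treatment based on UP will be the most efficient treatment and as effective as conventional psychological treatment". The same hypotheses place brief treatment below the combined arm on effect ("but less effective than “conventional psychological treatment plus pharmacological treatment").

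For the analysis, Proposed Analysis gives one sentence: "Last, we will estimate the Incremental Cost-Effectiveness Ratio (ICER) to compare the relationship between costs and effectiveness of different interventions". The article names no net benefit, dominance rule or plain cost comparison beside it.

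**The concern.** The ICER is the cost difference divided by the effect difference. The plan's central efficiency comparison sets the expected effect difference at zero, so the closer the hypothesis is to the truth, the worse the chosen measure behaves. Near zero the ratio jumps between large positive and large negative values on trivial changes in the denominator, has no stable mean, and usually has no bounded confidence interval.

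At stake is how the hypothesis of equal effect and better efficiency gets reported. If the ratio is the named result, the trial could confirm its own hypothesis and still print a number that does not express it. The reading of a sign-ambiguous ratio would then be chosen after the results are known.

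**Working it through.** **Arm sizes.** The article states no efficiency figure to reproduce, but the arm sizes can be checked. For a one-way ANOVA with five groups, f = 0.3 and alpha 0.05, the noncentrality is f² × N = 0.09 × 140 = 12.6. Power is 0.792 at N = 135 and 0.809 at N = 140, so 140 (28 per group) reproduces. Inflating for 15% dropout gives 140 / 0.85 = 164.7, hence 165 (33 per group). The sample size is not affected by this point.

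**Inputs for the ratio.**
- n = 28 or 33 per arm (Sample Size).
- True effect difference dE (brief minus conventional, in outcome SDs) = 0 (The Present Study; Anticipated Results).
- True cost difference dC (brief minus conventional) = -1 cost SD, varied from -0.5 to -2. This is an assumption, because the article gives no costs. The direction is plausible: Interventions gives 8 sessions for brief and 12 to 24 for conventional (4 to 16 fewer), both delivered by clinical psychologists in specialised care.
- Cost and effect uncorrelated (assumption).

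**Standard error of a standardised difference**, sqrt(2/n):
- n = 28: sqrt(2/28) = 0.267, 95% half-width 1.96 × 0.267 = 0.52.
- n = 33: sqrt(2/33) = 0.246, 95% half-width 0.48.

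**Behaviour of ICER = dC/dE.** With dC = -1 the ratio is -100 at dE = +0.01 and +100 at dE = -0.01. Across 400,000 simulated trials with true dE = 0 and dC = -1, n = 28:
- Brief is cheaper and better in 50% of trials and cheaper and worse in 50%. The sign of the ratio is a coin toss.
- The central 95% of the ratio runs from about -60 to +60. Analytic check with cost taken as known: 1 / (0.267 × 0.0627) is about 60. At n = 33 it is about -65 to +66.
- With a cost saving of 0.5 or 2 cost SDs (n = 28) the range is about ±30, or -117 to +120.
- Means over four batches of simulated trials were -34, 49, 1.5 and -1.5, so there is no stable mean.

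**Confidence set.** The Fieller 95% set is bounded only if |dE| / SE exceeds 1.96. At true dE = 0 that happens in 5% of trials, so the set is unbounded in about 95%. This does not depend on the assumed costs or on n.

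**Other comparisons.** The article does not hypothesise a zero effect difference for brief against TAU, minimum intervention or combined treatment. Against TAU at the planned d = 0.6 the true ratio is finite, although the denominator would be non-significant in 39% (n = 28) or 32% (n = 33) of trials. Against combined treatment, brief is expected to be less effective and is presumably cheaper. The ratio is then finite, but which arm is more efficient depends on whether it lies above or below a willingness-to-pay value.

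**Incremental net benefit** = λ × dE - dC, where λ is willingness to pay in cost SDs per outcome SD. Same assumptions, dC = -1, n = 28. The mean is 1.0 at every λ and the SD is 0.267 × sqrt(1 + λ²):

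| λ | SD | P(net benefit > 0) |
|---|---|---|
| 0 | 0.27 | 1.00 |
| 1 | 0.38 | 0.996 |
| 2 | 0.60 | 0.95 |
| 5 | 1.36 | 0.77 |

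At λ = 5, cost savings of 0.5 to 2 SDs give probabilities of 0.64 to 0.93. The quantity is finite and ordered at equal effect, and at λ = 0 it is a plain cost comparison.

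**The case against.** The strongest reply is that nothing is lost. An ICER cannot be computed without dC and dE, so both will be held. Read with its quadrant and a threshold, the ICER gives the same decision as the sign of net benefit. If brief is cheaper and dE is estimated just above zero, brief dominates. If dE is just below zero, the saving per unit of effect lost is very large. Both readings favour brief, so a coin toss in the sign is not a coin toss in the decision. This stands. A reader might infer that the efficiency claim cannot be decided from this trial; the documents do not support that. The trouble is in the ratio reported alone, and in its interval.

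It also stands that the ±60 range does not measure harm. It is in assumed cost units, and it widens slightly as the trial grows (±65 at 33 per arm).

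A reader might further infer a separate ICER for each of the seven outcome scales, or costs counted over unequal horizons because "the interventions included in the protocol are composed by a different number of sessions". The article states neither: it fixes no effect scale and no cost horizon for the ICER. The threshold, the interval method and the effect scale are details that a condensed article may leave to a fuller plan, and their absence is not held against it here.

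What the reply does not remove is the mismatch in the text. The one measure named has no value at the result hypothesised. Calling it equivalent to net benefit already brings in the quadrant and threshold that would make net benefit the better measure to name.

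**Conclusion.** The concern holds in a limited form. As the sole named efficiency measure, the ICER is badly matched to the hypothesis that brief is as effective as conventional treatment and more efficient. At a true effect difference of zero it is undefined. With 28 to 33 per arm its sign is positive or negative with equal probability, and its 95% confidence set is unbounded in about 95% of trials. Those two results need no cost figures; the numerical ranges for the ratio and for net benefit rest on the assumed cost differences and zero correlation.

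It would be too strong to say that the claim of being most efficient among five arms collapses. The zero denominator affects one of brief's four comparisons. For brief versus combined the issue is different and milder: if brief is the cheaper arm, a finite ratio needs a willingness-to-pay value before it ranks anything. This is a cheap improvement to a stated analysis and calls for no change to design, sample size or data collection.

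**What to change.** In Proposed Analysis, make incremental net benefit (λ × effect difference - cost difference) the quantity that decides efficiency, over a stated range of λ and with bootstrap 95% confidence intervals that resample each patient's cost and effect together. Report the cost difference and the effect difference separately with confidence intervals, above all for brief versus conventional. Keep the ICER as a descriptive summary for comparisons in which the effect difference is clearly non-zero.

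The cost is a little more analysis on the same patients and data, a change of wording, and the need to state a willingness-to-pay range on the chosen effect scale before results are seen. That range takes judgement, because symptom scales have no obvious monetary value. The λ = 0 end of the range, a plain cost comparison, needs no such judgement.

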## Anticipated Results

This research protocol pretends to highlight the importance of adapting treatments to real contexts of application, and their adjustment to brief formats of limited time that maximize the cost-benefit of implemented care, as other authors suggest (Kazdin, 2008; Moriana and Martínez, 2011), besides contributing to the dissemination of psychological treatments in primary and specialized care.

The principal objective of this work is to examine the effectiveness and the efficiency of the brief psychological treatment in a sample of patients with EDs, compared to other four treatments: conventional psychological treatment, conventional psychological treatment plus pharmacological treatment, minimum intervention based on basic psychoeducational information, and pharmacological treatment. Although we think that psychological treatment (brief and conventional) will be more effective than pharmacological treatment, as suggested by previous results with patients with EDs (Heuzenroeder et al., 2004; Watts et al., 2015), we expect that “conventional psychological treatment plus pharmacological treatment” will be the most effective treatment. This findings will be compliant with other studies that indicate that the combined treatment is superior in efficacy to CBT and pharmacotherapy alone in both anxiety disorders (Furukawa et al., 2007; Van Apeldoorn et al., 2008) and depression (Keller et al., 2000; Pampallona et al., 2004).

Due to brief psychological therapies have obtained similar results to conventional psychological therapies (Miller, 2000; Bloom, 2001; Lyons and Low, 2009; Nieuwsma et al., 2012), proving effective in reducing anxious-depressive symptoms (Koutra et al., 2010; Bernhardsdottir et al., 2013; Saravanan et al., 2017), and UP have demonstrated its effectiveness to the treatment of EDs (Barlow et al., 2004; Brown and Barlow, 2009; Farchione et al., 2012), we hope that brief psychological treatment based on UP will be the most efficient treatment and as effective as conventional psychological treatment. However, although there is evidence suggesting that the patient’s improvement, after being treated with brief psychological therapies, remains long after treatment (Hamdan-Mansour et al., 2009; Vázquez et al., 2012), some authors question the maintenance of long-term results (Seekles et al., 2013). Therefore, the results of this study will be added to the evidence of efficacy for brief psychological treatments for EDs right after the treatment and at 6-month follow-up.

By last, we think that “minimum intervention based on basic psychoeducational information, counseling and bibliotherapy” will be more effective than pharmacological treatment for participants included in this study, but will get worst results that different versions of psychological treatment. Due to this kind of interventions are not sufficiently represented in controlled research (Labrador et al., 2000), the results of this work could contribute to the dissemination of minimum psychoeducational interventions to address the treatment of EDs in the PC context.

In last years, new intervention modalities are gaining consensus for the treatment of mental disorders, such as the stepped care approach. This treatment modality consists of apply progressively low and high intensity interventions (Turpin et al., 2008) and is based in two fundamental principles. Firstly, the treatment should produce positive results with the least burden for the patient. Secondly, the results of the patients should be reviewed systematically to decide about the need to move to another level of treatment.

The stepped care model can be implemented in two different ways. Firstly, the purely stepped approach assigns low intensity treatment to all patients and proposes a more intense intervention for patients who do not benefit low intensity treatment. On the other hand, in the stratified approach, patients are initially assigned to different levels of intervention according to an assessment of the symptoms and risks presented (Turpin et al., 2008).

Some recent studies have proved the efficacy of the stepped care model for the treatment of mental disorders. For example, Salomonsson et al. (2018) examined the utility of a purely stepped approach for the treatment of EDs in a primary care setting. These authors showed that the 40% of patients improved with a low intensity treatment. Besides, with this model of treatment less than six sessions were needed per patient, obtaining an overall improve of 63%. Another study (Tasca et al., 2018) tested the usefulness of this approach of intervention for the treatment of binge eating disorder. The findings of this study indicated that the low intensity treatment reduced significantly the symptoms of patients and that a more intensive intervention did not reduce the symptoms more than the low intensity treatment.

In this line, if all the treatments included in our study prove to be effective for addressing EDs, may be used on a stepped care model ordered by the level of intensity. Thus, the minimum intervention based on basic psychoeducational information may be first step of the treatment, followed by brief psychological treatment, conventional psychological treatment and conventional psychological treatment plus pharmacological treatment.

## Limitations

This study presents several limitations. The first one is related to the design of the study, since the interventions included in the protocol are composed by a different number of sessions. Nevertheless, it is necessary to include interventions with different length to determine whether the treatment effect varies depending on the intensity and duration. Besides, except for the “brief psychological treatment based on UP” group, the number of sessions or weeks of interventions within a certain group could vary from one patient to another. However, we will make sure that each patient is evaluated 6 months after the end of the treatment (follow-up assessment).

As a limitation inherent in this type of studies, considerable dropout rate during the intervention process are expected, as well as a substantial missing data to follow-up. Nevertheless, participants will be animated by phone or email to continue with the treatment or to participate in the follow-up assessment. In addition, the anxious-depressive symptoms could be attenuated by the passage of time.

Other limitations may be related to the recruitment difficulties. Due to the participants must be diagnosed with a DSM-5 disorder and must meet predetermined cutoff points, may be recruitment problems related to the difficulty that participants completely met the eligibility criteria. Besides, patients may refuse to be treated by a different intervention than usual.

## Conclusion

This study describes an adaptation to brief format of the UP for the transdiagnostic treatment of EDs. If this RCT proves that brief psychological treatment is as effective as conventional psychological treatment and that both treatments are more effective than pharmacological treatment, the results of this RCT may encourage the implementation of brief therapies in the PC context. This implementation could lead to the decongestion of the public health system, the treatment of a greater number of people with EDs in a shorter time, the reduction of the side effects of pharmacological treatment and a possible economic savings for public purse.

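### The planned analysis and sample size cannot support a conclusion that brief treatment is as effective as conventional treatment; the plan should estimate the difference with its 95% CI

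*Protocol article*

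**What the plan says.** The Present Study section hypothesises that brief treatment will match conventional treatment in effectiveness while being more efficient. Anticipated Results repeats this: "we hope that brief psychological treatment based on UP will be the most efficient treatment and as effective as conventional psychological treatment". The Conclusion begins "If this RCT proves that brief psychological treatment is as effective as conventional psychological treatment" and joins it to a second condition, that both treatments are more effective than pharmacological treatment. If both hold, the results may encourage implementation of brief therapies in primary care.

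Proposed Analysis says that "to examine longitudinal changes over time (baseline, posttreatment and follow-up) and between-group differences on these changes we will use linear mixed models", on an intention-to-treat and a per-protocol basis, with Cohen's d for between-group effects and an incremental cost-effectiveness ratio.

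Under Sample Size, d = 0.6 "was assumed to detect differences between the interventions and TAU". It was converted to f = 0.3, and "we established the sample size for analysis of variance". With power 0.80 and alpha 0.05 this gives 140 participants (28 per group), raised to 165 (33 per group) for 15% dropout.

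**The concern.** To conclude that one treatment is as effective as another, the data must rule out a loss that would matter. A test for a difference does not do that: in a small comparison it is often non-significant whether or not a difference exists. The article fixes a difference analysis and a sample size, and neither was built for brief versus conventional treatment. Its Conclusion nevertheless speaks of proving equal effectiveness for that pair.

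At stake is a stated hypothesis and one of the two conditions for the implementation message. The efficiency argument leans on it too, since brief treatment is expected to be equally effective and more efficient. If a non-significant result were reported as equal effectiveness, readers would take the absence of a detected difference as evidence that little is lost by shortening therapy.

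**Working it through.** **Inputs from Sample Size:** f = 0.3, d = 0.6 versus TAU, alpha 0.05, power 0.80, 28 evaluable and 33 randomised per arm, 15% dropout. **Assumptions not in the article:** a baseline-to-outcome correlation of 0.5 as the favourable case, the margins used below, and the reading of 0.6 SD as the benefit of conventional treatment over TAU.

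**1. The plan's own figure.** For a one-way ANOVA with five groups, the noncentrality is N × f² = 140 × 0.09 = 12.6 on 4 and 135 degrees of freedom. Power is 0.809. The smallest N reaching 0.80 is 138, which balances to 140. Then 140 / 0.85 = 164.7, so 165. The figures reproduce, but they are for the omnibus test.

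**2. Precision for brief minus conventional (SD units).** SE = √(2/n), multiplied by √(1 − r²) if baseline is used. Half-width = 1.96 × SE, or the t quantile × SE.

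| Case | SE | 95% half-width (z to t) | Share of 0.6 SD |
|---|---|---|---|
| 28 per arm, unadjusted | 0.267 | 0.52 to 0.54 | 87 to 89% |
| 33 per arm, unadjusted | 0.246 | 0.48 to 0.49 | 80 to 82% |
| 33 per arm, r = 0.5 | 0.213 | 0.42 to 0.43 | 70 to 71% |

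These shares apply when the observed difference is exactly zero. At 28 per arm, unadjusted, an observed deficit just short of significance has a limit near 2 × 0.536 = 1.07 SD.

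**3. Chance of a non-significant difference when brief is truly worse (two-sided 0.05).**
- 28 per arm, unadjusted (noncentral t): 80% for a 0.3 SD deficit, 40% for 0.6 SD.
- 33 per arm, unadjusted (noncentral t): 78% and 33%.
- 33 per arm, r = 0.5 (normal approximation): 71% and 20%.

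**4. Power of a margin-based test if the two are truly equal (one-sided 0.025).** Power = Φ(margin/SE − 1.96).
- Margin 0.3 SD: Φ(0.3/0.267 − 1.96) = 20% at 28 per arm; Φ(0.3/0.213 − 1.96) = 29% at 33 per arm with r = 0.5.
- Margins 0.5 and 0.6 SD at 28 per arm: 46% and 61%.
- Margin testable with 80% power, (1.96 + 0.8416) × SE: 0.75 SD at 28 per arm, 0.69 at 33, and 0.60 at 33 with r = 0.5. The last equals the whole assumed benefit.
- Evaluable patients per arm needed for 80% power at a 0.3 SD margin: 2 × 2.8016² / 0.09 = 174.4, so 175 (about 131 with r = 0.5).

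**5. The full condition in the Conclusion.** I simulated three arm means with conventional treatment 0.6 SD better than TAU. The condition counted as met when brief versus conventional was non-significant and both were significantly better than TAU.
- 28 per arm, unadjusted: about 16 to 17% for a true 0.3 SD deficit and 2% for 0.6 SD.
- 33 per arm, r = 0.5: about 24% and 2%.

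**The case against.** A reader might infer from the 80% and 40% figures that an inferior brief therapy would probably be recommended for roll-out. The document does not support that. Those figures describe one pairwise test, whereas the Conclusion also requires both treatments to beat pharmacological treatment, and step 5 shows how much this lowers the chance. The wording there is also conditional, and Anticipated Results speaks of hope.

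Nor does any passage say that a non-significant result will be read as equality. The mixed models yield estimates, and Cohen's d is planned. That stands: the misreading is one that the plan leaves open, not one that it announces.

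A further objection is that a margin and a confidence-interval rule can sit in a full protocol or SAP that is not shown. The absence of a margin from the article is therefore not itself the point. But a margin set elsewhere could not rescue the claim at the sample size fixed here, because none at or below half of the assumed benefit can be tested with useful power.

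Finally, the unadjusted figure at 28 per arm is the pessimistic end, since the mixed model uses baseline and the intention-to-treat set includes all randomised patients. This is fair, and a range is given for that reason. The favourable end still leaves about 70% of the assumed benefit unexcluded. Limitations expects considerable dropout and substantial missing follow-up data, which works against reaching that end.

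**Conclusion.** The concern holds for the equal-effectiveness claim. With the stated analysis and 28 to 33 patients per arm, a non-significant difference between brief and conventional treatment cannot support it. Even an observed difference of zero leaves a loss of about 0.42 to 0.54 SD inside the 95% CI, against an assumed benefit of 0.6 SD. The concern does not extend to a probable wrongful roll-out, for which the chance is about 16 to 17% (0.3 SD deficit) or 2% (0.6 SD deficit) at 28 per arm.

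These sizes rest on normal outcomes with equal variances, on 0.6 SD as the benefit of conventional treatment over TAU, and, at the favourable end, on a baseline correlation of 0.5 that the article does not give. The conclusion is the same across the range examined.

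**What to change.** In The Present Study, Anticipated Results and the Conclusion, replace the language of proving or expecting equal effectiveness with estimation of the brief minus conventional difference and its 95% CI, in the intention-to-treat and per-protocol sets. In Proposed Analysis, add that p > 0.05 for this comparison will not be read as equal effectiveness.

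If the sponsor wants to keep the claim, it should prespecify and justify a margin, draw the conclusion only if the 95% CI excludes a loss of that size, and disclose the power. For an illustrative margin of 0.3 SD (half of the assumed benefit) that is about 20 to 29%, so the claim would usually fail even if the treatments were equal. Estimation is the more practical choice.

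The cost is wording only, with no extra patients. The downside is that the trial gives up or qualifies a claim that its size cannot support.
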